## Abstract

**Introduction:**

Neurosurgery for brain tumors needs to find a complex balance between the effective removal of targeted tissue and the preservation of surrounding brain areas. Neuromodulation-induced cortical prehabilitation (NICP) is a promising strategy that combines temporary inhibition of critical areas (virtual lesion) with intensive behavioral training to foster the activation of alternative brain resources. By progressively reducing the functional relevance of targeted areas, the goal is to facilitate resection with reduced risks of neurological sequelae. However, it is still unclear which modality (invasive vs. non-invasive neuromodulation) and volume of therapy (behavioral training) may be optimal in terms of feasibility and efficacy.

**Methods and analysis:**

Patients undertake between 10 and 20 daily sessions consisting of neuromodulation coupled with intensive task training, individualized based on the target site and neurological functions at risk of being compromised. The primary outcome of the proposed pilot, single-cohort trial is to investigate the feasibility and potential effectiveness of a non-invasive NICP protocol on neuroplasticity and post-surgical outcomes. Secondary outcomes investigating longitudinal changes (neuroimaging, neurophysiology, and clinical) are measured pre-NICP, post-NICP, and post-surgery.

**Ethics and dissemination:**

Ethics approval was obtained from the Research Ethical Committee of *Fundació Unió Catalana d'Hospitals* (approval number: CEI 21/65, version 1, 13/07/2021). The results of the study will be submitted to a peer-reviewed journal and presented at scientific congresses.

**Clinical trial registration:**

ClinicalTrials.gov, identifier NCT05844605.

## Introduction

Neurosurgeons performing surgery for brain tumors face a complex dilemma: On the one hand, they must achieve the complete eradication of the tumor; on the other hand, they must preserve the healthy brain tissue surrounding the tumor (1). In fact, radical approaches have the advantage of removing a higher percentage of the tumor, but at the cost of increased risk for post-surgery functional impairments; more conservative approaches have less risks of functional deficits but expose patients to an increased likelihood of developing secondarities. In the last few years, it has been proposed to apply a conditioning intervention before surgery (prehabilitation) to modulate neuroplasticity (2, 3), called neuromodulation-induced cortical prehabilitation (NICP) (4). The objective was to reduce the functional relevance of brain areas close to the tumor (critical areas) in favor of a more distributed brain network, functionally associated with the targeted area but anatomically distant from the tumor. This way, neurosurgeons may apply a more radical approach without the associated risk of functional impairments; from this perspective, it is argued that NICP could represent the optimal therapeutic intervention before intraoperative cortical–subcortical mapping to tailor the resection up to the functional boundaries (hopefully widened by previous neuroplastic changes induced with NICP) (3).

Pioneering efforts have been made in the field, with the publication of four articles (three case reports and one case series) where NICP was undertaken by a total of seven patients with brain tumor (2, 5–7). A common element was neuromodulation coupled with behavioral training: Neuromodulation provokes temporary inhibition (virtual lesion) of eloquent areas, while behavioral training (cognitive/speech or motor training) promotes the activation of alternative brain resources. By performing several sessions of intensive neuromodulation and task-specific training, long-term depression and long-term potentiation mechanisms determine the consolidation of neuroplastic changes before surgery (4, 8).

Notably, NICP by means of *non-invasive* neuromodulation was applied in only one patient, the first case report of NICP published by Barcia et al. (5). The patient (a 59-year-old woman) presented with dysnomia and was diagnosed with left-sided precentral oligodendroglioma (WHO II); during the first brain surgery, the tumor could not be completely removed because of the presence of active language areas. Nine months later, symptoms worsened because of tumor progression. Therefore, before a second surgery, the patient received 13 daily sessions of NICP, consisting of continuous repetitive transcranial magnetic stimulation (rTMS) over Broca's area immediately followed by 10 min of intensive speech training. MEG showed greater bilateralization during speech production, while fMRI with a similar paradigm did not show any change. Language function was temporarily affected after each rTMS session and improved over basal values after each speech training session; along the experiment language function improved, with rTMS having a progressively lower impact. Transient language deficits were present after the second surgery, recovered after 3 weeks, but did not achieve preoperative scores. Surgery was not performed with radical intent, given that an intraoperative biopsy indicated radiation necrosis. Afterward, the patient developed secondarities and died 3 months later.

Since this first case report, it has been inferred that NICP could promote neuroplastic and behavioral changes, but also that higher dosages or different modalities of intervention may have been required (5). In line with these hypotheses, subsequent studies applied radically different NICP protocols, where *invasive* neuromodulation (extraoperative direct cortical stimulation) was applied continuously (24 h a day) at maximal tolerable intensity, with the goal of inhibiting eloquent areas within or near the tumor. In a case series of five patients, Rivera et al. (2) performed first brain surgery, followed by NICP over 15–25 days of therapy, and finally a second surgery (2). During the first surgery, neurosurgeons removed as much tumor mass as possible based on results from cortical and subcortical intraoperative stimulation mapping, while at the same time implanting a grid of subdural electrodes for intracranial electrical stimulation. The subsequent NICP protocol consisted of continuous intracranial stimulation over eloquent areas to inhibit their functionality (virtual lesion), while at the same time providing intensive behavioral training (several hours a day) to patients, to foster the activation of associated functional networks. After several weeks of prehabilitation, a second surgery was performed, where neurosurgeons removed the grid of electrodes and sought to eradicate an additional tumor mass. Results were promising: there was a marked reduction in the functional relevance of eloquent areas, so that during the second surgery, neurosurgeons could remove an additional percentage of tumor mass, without any permanent deficit. However, the main limitations were the need to perform two surgeries and the relatively high rate of adverse events (focal seizure, osteomyelitis, epidural abscess, intermittent myoclonus, and subdural hematoma) caused by surgery and by the presence of intracranial electrodes. More recently, Serrano-Castro et al. (7) published a case report of a 17-year-old patient with a neuroepithelial dysembryoblastic tumor in the left temporo-parietal region provoking refractory focal motor seizures (7), who undertook a similar protocol as described by Rivera-Rivera et al. (2) (first surgery, placement of intracranial electrodes for invasive neuromodulation during subsequent prehabilitation, and second definitive surgery to remove the tumor and the electrodes). However, the first craniotomy was intended specifically for placing electrodes, and NICP was performed for only 6 days, during which language training was provided very intensively (6 h a day). The outcomes were the development of functional activation in the homologous right Wernicke's area and no residual motor language function over the tumor region. Such neuroplastic changes made possible to perform complete tumor eradication, and the patient has since then (at least 1 year) been seizure-free, with no neurological symptoms.

To summarize, seminal results from previous studies indicate that NICP is capable of clinically meaningful neuroplastic changes, although the optimal modality and dosage of therapy remain to be elucidated (4). On the one hand, invasive modalities allow intensive and prolonged inhibition of cortical activity over targeted areas, resulting in meaningful neuroplastic changes, but at the cost of additional surgery and an increased rate of adverse events (2). On the other hand, non-invasive neuromodulation is relatively safe and feasible but has shown less convincing results regarding neuroplasticity (5). However, non-invasive NICP was investigated in only one patient receiving a small, and perhaps insufficient, volume of intervention; further cohort studies exploring different neuromodulation modalities and higher volumes of therapy are needed to determine the feasibility and effectiveness of non-invasive NICP (3, 4).

Therefore, the objectives of the present single-cohort, pilot feasibility trial were to investigate the feasibility (primary outcome) and effectiveness (secondary outcome) of a NICP protocol before brain surgery, consisting of daily sessions of non-invasive neuromodulation over critical areas, followed by intensive behavioral training. We include patients with brain tumors requiring elective neurosurgery. By performing non-invasive neuromodulation within safety guidelines (9), we hypothesize that the protocol is safe and well-tolerated by subjects, with no adverse events and high adherence to the treatment. Second, by comparing neural correlates pre- vs. post-prehabilitation, we will determine whether the intervention is effective in promoting a functional reorganization of the brain, similar to what has already been demonstrated for therapeutic applications of neuromodulation in stroke and other neurological disorders (10). Finally, we will report outcomes post-surgery and the individual's evolution in the long-term recovery phase. The main results will be disseminated by publishing an open-access original research article on the feasibility and effectiveness of non-invasive prehabilitation in neuro-oncology. Furthermore, we will create an online database of case reports with detailed information regarding prehabilitation, surgery, post-surgery rehabilitation, and the long-term evolution of each patient to inform the international community of neurosurgeons and other clinicians in the neurological field.

## Methods and analysis

A schematic of the study protocol is outlined in Figure 1. The whole protocol has been developed according to the SPIRIT 2013 guidelines for protocols of clinical trials (11, 12).

**Figure 1 F1:**
[figure not shown]
Schedule of enrollment, interventions, and assessments. Interventions at each time point of the study period: -t1 (enrollment): eligibility screen, informed consent, and baseline evaluation. t0 (allocation): fMRI and TMS mapping to determine whether to allocate patients in the prehabilitation program for upper limb or language training; baseline evaluation, if not performed at -t1; assessment of mobility, independency, and quality of life. t1: assessment before starting the prehabilitation protocol; assessment of clinical outcomes related to upper limb or language/cognitive function. t2: first session of prehabilitation. t3: last session of prehabilitation. t4: assessment after the end of the prehabilitation protocol; assessment of clinical outcomes related to the intervention, mobility, independency, quality of life, fMRI, and TMS mapping. t5: surgery. t6: surgical outcomes: intraoperative brain mapping, amount of tumor removed, adverse events, and post-surgery symptoms.

### Study settings

Patients on the waiting list for brain surgery are referred by neurosurgeons involved in the study. The principal investigator ([name]) obtains written informed consent from patients wishing to be enrolled. Participants undertake an articulated, multidisciplinary protocol consisting of clinical, neurophysiological, and neuroimaging assessment, non-invasive brain stimulation, and intensive neurorehabilitation before surgery, neurosurgery, and neurorehabilitation post-surgery. Clinical assessments, neurophysiological investigations, and the whole prehabilitation program are performed at the *Guttmann Institute (Guttmann Barcelona – Brain Health and Neurorehabilitation, Barcelona, Spain)*. Neuroimaging assessment is performed at the *Unitat d'Imatge per Ressonància Magnètica IDIBAPS (Institut d'Investigacions Biomèdiques August Pi i Sunyer) at Hospital Cl*í*nic de Barcelona, Barcelona*. Neurosurgery is performed at the hospitals where the neurosurgeons involved in the study operate. Post-surgery neurorehabilitation is provided at the *Guttmann Institute (Institut Guttmann, Badalona, Spain)*.

### Eligibility

Inclusion criteria are as follows: adults (age ≥ 18 years old) with a diagnosis of brain tumor requiring neurosurgery; ability to undertake at least 10 sessions of the prehabilitation protocol; tumor location posing the patient at risk of developing post-operative neurological deficits, for instance at the level of upper limb motor function and speech production; ability to understand the general purpose of the prehabilitation program and understand simple instructions; being willing to participate and sign the informed consent; being able to sit unassisted for 1 h.

Patients are excluded in cases of any contraindication for magnetic resonance imaging or transcranial magnetic stimulation (9); unstable medical conditions; musculoskeletal disorders that may significantly affect functional training; severe speech and/or cognitive impairment; pain, depression, and fatigue that may significantly affect functional training; and a history of alcohol/drug abuse.

### Primary and secondary outcomes

The primary outcome is the feasibility of the whole intervention, defined by the following parameters:

- Adherence to treatment: to define that the patient completed the protocol, at least 75% of the planned sessions should be performed.- Retention: successful retention rate is reached if at least 75% of enrolled participants complete the prehabilitation program.- Adverse events: absence of any adverse event attributable to the prehabilitation program, except for expected transient mild symptoms previously reported for neuromodulation (headache, syncope, and skin irritation) or motor training (mild pain and fatigue).- Patient's satisfaction: At the end of the protocol, participants fill out questionnaires evaluating the patient's satisfaction with the treatments received (13).

Secondary outcomes are related to exploratory analyses of the effectiveness and potential mechanisms of action of the proposed intervention. We investigate changes from baseline regarding clinical outcomes, fMRI, and TMS mapping. Notably, the goal of the intervention is to reduce the functional relevance of targeted areas because of compensatory activation of other brain resources within the same functional network. Slow-growing tumors already demonstrated that similar neuroplastic changes may occur, with the tumor mass progressively interfering with the functionality of critical areas, while remote brain areas increase their activation; such compensatory mechanisms may explain why these types of tumors are asymptomatic and without any functional deficits in the initial phases (14, 15). From this perspective, the prehabilitation program could be considered a method to artificially optimize and accelerate this neuroplastic adaptation for therapeutic purposes (3). Therefore, we do not expect significant changes regarding clinical outcomes, whereas we consider changes in neuroimaging and neurophysiology outcomes as indicators for the effectiveness of the prehabilitation program.

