### Discontinuation, adherence, permission for concomitant care, ancillary, and post-trial care

Intervention is discontinued at the participant's request or in case of adverse events attributable to neuromodulation (seizure). Adherence to treatment is monitored by recording the rate of sessions attended over the total number of planned sessions.

Patients are allowed to undertake any concomitant care during the intervention if it does not interfere with the schedule of the prehabilitation program. However, we also recommend patients avoid other neuromodulation or motor skill training approaches, as they may be counterproductive to the desired outcome of the intervention. For instance, undertaking additional upper limb training sessions outside the prehabilitation protocol may reinforce the activation of peritumoral areas, as the inhibitory effect of neuromodulation might not be present anymore.

In case of post-surgery cognitive and/or neurological deficits, neurorehabilitation (usually 10 to 30 sessions) will be provided by the Guttmann Institute as a service offered to patients who have participated in the research study.

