### Dissemination

A summarized version of the study protocol has been published online with ClinicalTrials.gov Identifier NCT05844605 (more information of the SPIRIT WHO trial registration data set are reported in Table 1).

**Table 1 T1:** SPIRIT WHO trial registration data set.

**Data category**	**Information**
Primary registry and trial identifying number	ClinicalTrials.gov (NCT05844605)
Date of registration in primary registry	04/05/2023
Secondary identifying numbers	Protocol ID 2020330
Source(s) of monetary or material support	Fundación Joan Ribas Araquistain (reference project 2020.330) Fundaciò La Maratò De TV3 (reference project 201735.10) Fundaciò Bancària La Caixa (reference project LCF/PR/PR16/11110004)
Primary sponsor	Institut Guttmann, Institut Universitari de Neurorehabilitació adscrit a la UAB, Badalona, Spain
Contact for public or scientific queries	Name: [name] Email address: [contact] [contact] Postal address: [name]
Title	Neuromodulation-Induced Prehabilitation to leverage neuroplasticity before surgery for brain tumors: protocol for a single-cohort feasibility trial.
Countries of recruitment	Spain
Health condition(s) or problem(s) studied	Primary brain tumor
Intervention(s)	Neuromodulation, behavioral training, neurosurgery
Key inclusion and exclusion criteria	Inclusion: diagnosis of primary brain tumor requiring neurosurgery Exclusion: contraindications to TMS or MRI
Study type	Single-arm pilot feasibility trial
Date of first enrollment	21 June 2021
Target sample size	20
Recruitment status	Recruiting
Primary outcome(s)	Feasibility
Key secondary outcomes	Changes pre-/post-intervention on clinical, neurophysiology, and neuroimaging outcomes

Study data are collected and managed using REDCap electronic data capture tools hosted at Guttmann Institute (76, 77). To ensure confidentiality, each study participant is identified with an alphanumerical code. Data from neurophysiology and neuroimaging are anonymized and stored on online cloud platforms. Accessibility to data files is granted by the principal investigator only to researchers involved in data management. The hard copy of informed consent forms and other data collected on paper is stored in a locked closet at the Guttmann Institute, accessible only by the principal investigator.

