### Statistical analysis

We use R software for statistical analysis and graphics (78). Given the small sample size (20 patients, based on a realistic estimate of the recruitment rate) and the use of ordinal scales, we perform non-parametric statistics. For descriptive reporting of continuous/ordinal variables, median and interquartile range (IQR) are used to indicate measures of central tendency and dispersion, respectively; frequencies are reported by indicating the absolute value, followed by the relative value (percentage) in brackets; in case of binary variables (such as gender), only one of the two variables is reported. For the primary analysis (feasibility), we report descriptively whether we met the criteria for recruitment, retention, and adverse events; adherence to treatment (both neuromodulation and behavioral training) is reported as the median (IQR). An exploratory analysis of effectiveness is conducted by performing a repeated-measure comparison (pre- vs. post-prehabilitation). Together with reporting the estimates of treatment effect, we indicate the actual level of significance (two-sided *p*-value) and 95% confidence interval (79). For quantitative and ordinal variables, we use Wilcoxon signed-rank test. For dichotomous variables, we use McNemar's test. For correlations between quantitative/ordinal variables measured at the same time point, we use Kendall's tau rank correlation coefficient. To explore prediction models, we use simple and multiple linear regression analyses for continuous/ordinal outcomes and simple and multiple logistic regression for binary outcomes. In case of missing data, we perform pairwise deletion. Further explorative analysis may include big data analysis of neuroimaging/neurophysiology data.

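### The primary feasibility outcome is judged by point-estimate cut-offs in 20 patients with no confidence intervals, and its adverse-event criterion counts only attributable, non-exempt events

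*Protocol article*

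**What the plan says.** The Protocol article makes feasibility the primary outcome and defines it by four parameters under Primary and secondary outcomes. Three matter here.

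- **Adherence.** A patient counts as having completed the protocol if "at least 75% of the planned sessions should be performed".
- **Retention.** The rule is that a "successful retention rate is reached if at least 75% of enrolled participants complete the prehabilitation program".
- **Adverse events.** The criterion is "absence of any adverse event attributable to the prehabilitation program, except for expected transient mild symptoms". Syncope is one of the symptoms named in the exemption, along with headache, skin irritation, mild pain and fatigue.

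The Statistical analysis section says of the primary analysis that "we report descriptively whether we met the criteria", naming recruitment, retention and adverse events, with adherence given as a median and interquartile range. The 95% confidence interval appears only afterwards, with the treatment-effect estimates of the exploratory comparison before and after prehabilitation. The same section bases the sample of 20 on expected recruitment.

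The Introduction states the safety expectation more broadly: "we hypothesize that the protocol is safe and well-tolerated by subjects, with no adverse events and high adherence to the treatment". It mentions no exemption.

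**The concern.** The outcome that decides whether the programme is worth pursuing is the one given no measure of precision, while the exploratory outcomes do get intervals. With 20 patients, a criterion that is just met says little about the true rate, and a count of zero events is compatible with a risk that would matter.

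The adverse-event result also passes through two filters before anything is counted: attribution to the programme, and the exemption for expected mild symptoms. Attribution is hard for seizures in this population. The section on discontinuation names seizure as the adverse event attributable to neuromodulation, yet one of the case reports in the Introduction concerns a patient whose tumour caused refractory seizures. In a single-cohort trial everyone receives the intervention, so the assessor cannot be blinded to it and there is no comparator rate against which to check the judgement. If only the filtered count is reported, readers cannot see how much depends on the filters.

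**Working it through.** **Inputs.** N = 20 (Statistical analysis, and the registration table: "Target sample size 20"). The retention threshold is 75% of enrolled patients, and the adverse-event threshold is zero countable events (both from Primary and secondary outcomes). The true rates used below are assumptions, shown as ranges. Twenty patients are assumed to be enrolled and assessed.

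**Sample size.** The figure of 20 cannot be re-derived. It rests on recruitment, and the article gives no null rate, error rate or precision target for the primary outcome.

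**Retention rule as a count.** 0.75 × 20 = 15, so the rule is met from 15/20 upwards.

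**Exact (Clopper-Pearson) 95% interval for x of n.** Lower limit = 2.5% quantile of Beta(x, n − x + 1). Upper limit = 97.5% quantile of Beta(x + 1, n − x).

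| Retained | Exact 95% CI |
|---|---|
| 15/20 | 50.9% to 91.3% |
| 17/20 | 62.1% to 96.8% |
| 18/20 | 68.3% to 98.8% |
| 19/20 | 75.1% to 99.9% |

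The Wilson interval for 15/20, as a check, is 53.1% to 88.8%. The exact lower limit first exceeds 75% at 19/20.

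**Chance of meeting the retention rule.** P(X ≥ 15) with X ~ Binomial(20, p):

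| Assumed true retention p | P(pass) |
|---|---|
| 60% | 12.6% |
| 65% | 24.5% |
| 70% | 41.6% |
| 75% | 61.7% |
| 80% | 80.4% |
| 85% | 93.3% |

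**Zero adverse events in 20.** Two-sided 95% upper limit = 1 − 0.025^(1/20) = 16.8%. One-sided 95% upper limit = 1 − 0.05^(1/20) = 13.9%. If only 15 patients received the full programme, the two-sided limit would be 21.8%.

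The probability of seeing no event at a true per-patient risk q is (1 − q)^20:

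| Assumed risk q | P(0 of 20) |
|---|---|
| 1% | 81.8% |
| 2% | 66.8% |
| 5% | 35.8% |
| 10% | 12.2% |

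**What the count covers.** These figures apply only to events that are both attributed to the programme and not exempt. Events outside that set do not affect whether the criterion is met. The Introduction's hypothesis covers adverse events without restriction, so meeting the criterion would not by itself confirm the hypothesis.

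**The case against.** The strongest reply is that this is a pilot feasibility trial and descriptive progression criteria are normal in one. Frequencies will be reported as counts with percentages, so any reader can compute an interval. That stands as far as it goes: no analysis is invalid, and neither a hypothesis test nor a larger sample is called for. It does not explain why the exploratory estimates receive intervals and the primary proportions do not. Nor is this a detail left to a separate analysis plan, because the article itself states how the primary outcome is analysed.

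Several stronger readings are tempting, and the documents do not support them.

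- *The trial will declare the programme safe.* No section plans such a declaration. Safety is stated as a hypothesis, and adverse events are one part of feasibility.
- *The criterion could be met with every patient having syncope.* The exemption is limited to symptoms that are expected, transient and mild, so a severe episode is not clearly exempt. The text sets no limit on the number of exempt episodes, but that is silence and not permission.
- *Seizures will be put down to the tumour.* Nothing says so, and the discontinuation section links seizure to neuromodulation. The point is only that attribution is uncertain. The procedure for it may well be in the full protocol.
- *The retention rule is a coin flip.* Any cut-off passes about half the time when the true rate lies at the cut-off. Away from it the rule does discriminate, with 12.6% passing at 60% and 93.3% at 85%.

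For events that do count, the zero-event rule is strict: at a true risk of 5% it fails 1 − 0.358 = 64.2% of the time.

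**Conclusion.** The concern holds as a matter of precision and of what is counted. Reported as planned, a retention pass at 15/20 is compatible with true retention anywhere from 50.9% to 91.3%, and a clean adverse-event result does not exclude a risk of up to 16.8%. The adverse-event result further depends on an attribution judgement made without blinding or a comparator, and on an exemption that the Introduction's hypothesis does not share.

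This rests on 20 patients being enrolled and on the exact binomial model. It does not show that the trial is unsound or that its criteria are wrong for a pilot. It limits what a met criterion can be taken to mean. Which symptoms ought to be exempt is a clinical matter and is not judged here.

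**What to change.** **Statistical analysis.** Report the proportion retained, among all enrolled, and the proportion of patients with an adverse event, each with an exact (Clopper-Pearson) 95% confidence interval. State that meeting the criteria supports further testing, and does not establish that retention is at least 75% or that the programme is safe. Adherence can stay as a median with interquartile range.

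**Primary and secondary outcomes.** Keep the attributable criterion. Beside it, report all adverse events regardless of attribution or exemption, with seizures and syncope shown separately. The window should run from the first TMS exposure, which Figure 1 places at the t0 mapping, up to surgery. Starting at the first prehabilitation session would miss the baseline mapping, and stopping at the post-prehabilitation assessment would miss the interval before surgery. Base any safety statement on both counts.

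**Introduction.** Reconcile the hypothesis of no adverse events with the exemptions in the criterion.

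**Cost.** A few sentences, with no additional patients and no change to any clinical rule. The reported figures will look less favourable. All-cause counts will include tumour-related events, with no comparator to separate them, which is why both counts are needed. Every event must be logged before it is attributed; the article does not say explicitly that this is done, so it should be confirmed.

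### Satisfaction, part of the primary outcome, has one stated collection time, the end of the protocol; nothing secures answers from patients who discontinue, or collection before surgery

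*Protocol article*

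**What the plan says.** Under Primary and secondary outcomes, the Protocol article states: "The primary outcome is the feasibility of the whole intervention, defined by the following parameters". Four parameters follow: adherence, retention, adverse events and satisfaction.

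- **Satisfaction.** The timing is given once: "At the end of the protocol, participants fill out questionnaires". No threshold and no summary measure are attached.
- **Completion.** The adherence item sets the rule for calling a patient a completer: "to define that the patient completed the protocol, at least 75% of the planned sessions should be performed".
- **Retention.** The criterion is set over everyone who enters the trial: "successful retention rate is reached if at least 75% of enrolled participants complete the prehabilitation program".

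The section on discontinuation and adherence allows the intervention to stop when the participant asks, or for an adverse event attributed to neuromodulation. It describes no assessment at that point.

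The Statistical analysis section gives the sample size as "20 patients, based on a realistic estimate of the recruitment rate" and applies pairwise deletion to missing data. Its sentence on the primary analysis names recruitment, retention, adverse events and adherence, but not satisfaction.

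The Figure 1 legend lists the assessments at t4 (after prehabilitation, before surgery at t5) and at t6 (surgical outcomes). Satisfaction appears under neither; the figure itself is not available.

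**The concern.** A feasibility trial needs to hear from the patients for whom the programme was too burdensome. Some who withdraw at their own request may be among them. If the questionnaire is tied to a point that such patients do not reach, and missing answers simply drop out, the satisfaction summary describes those who stayed. It can then look good while the programme is losing patients.

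Timing relative to surgery is a second, smaller matter. If some patients answer after surgery, its result may colour a rating meant for the prehabilitation.

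Both points concern data collection. An analysis plan written later cannot recover an opinion that was not asked for when the patient left.

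**Working it through.** The article states no expected satisfaction figure, so there is nothing to reproduce. The check asks how many scores could be absent and how far that could move a summary.

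**Inputs from the article:** N = 20 enrolled (Statistical analysis); retention succeeds if at least 75% complete; a completer has performed at least 75% of planned sessions (both under Primary and secondary outcomes); 10 to 20 sessions are planned (Interventions).

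**Step 1: fewest completers that meet the retention criterion.** 0.75 × 20 = 15, so up to 20 − 15 = 5 patients (25%) may be non-completers in a trial that counts as retained.

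**Step 2: are non-completers the same as early leavers?** Not exactly. With 10 planned sessions, 0.75 × 10 = 7.5, so 8 are needed. A patient who attends 7 of 10 spread over the whole schedule is a non-completer but reaches the end and can answer. A patient who stops for good after 8 of 10 is a completer but has left early. So 5 is an upper bound on non-completers without a score, reached only if all five leave early and none is asked. Completers who stop late are outside that count.

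**Step 3: effect on a summary.** Two assumptions are made for illustration only: satisfaction is scored yes/no, and only completers answer. The article specifies neither. With k responders, of whom s are satisfied, the observed proportion is s/k. The proportion over all enrolled lies between s/20 (no non-responder satisfied) and (s + 20 − k)/20 (all satisfied).

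| Responders k | Satisfied s | Observed s/k | All enrolled, lowest to highest |
|---|---|---|---|
| 15 | 15 | 100% | 75% to 100% |
| 15 | 14 | 93.3% | 70% to 95% |
| 15 | 12 | 80% | 60% to 85% |
| 18 | 18 | 100% | 90% to 100% |
| 20 | 20 | 100% | 100% |

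In the second row, if 1 of the 5 non-responders were satisfied (assumed), the figure for all enrolled would be (14 + 1)/20 = 75%.

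The overstatement s/k − s/20 is largest when s = k, where it equals 1 − k/20: 25 percentage points with 15 responders, 10 with 18, and 0 with 20.

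**Step 4: timing relative to surgery.** The adherence item defines completing the protocol by sessions performed, which points to the end of prehabilitation. The Figure 1 legend specifies prehabilitation when it places t4. Study settings, however, describes a protocol that also includes neurosurgery and rehabilitation afterwards. The satisfaction item names no visit, so both readings remain open, with the pre-surgery one more likely.

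**The case against.** The strongest reply is that the article nowhere excludes early leavers. It says that participants fill out the questionnaires, and the end of the protocol can mean the end of each person's own participation. A journal article commonly leaves withdrawal procedures to the full protocol, which is not shown. This stands. A reader might infer that early leavers are not asked and that the result is a completers-only figure, but the text supports only that no collection is stated for them.

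A reader might also infer that satisfaction could never count against feasibility. That does not follow. Dissatisfied patients who finish would still lower the rating, and drop-out counts separately through retention, whose denominator is everyone enrolled. What leaves satisfaction without a pass/fail role is that no criterion is set for it. That is a separate matter, which changing the collection time would not settle.

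Nor would the trial report 93%, or any other percentage, on the present text. The article's general rule for continuous and ordinal variables is median and interquartile range, and it plans no yes/no scoring. It also gives no data showing that those who leave are less satisfied; that is plausible but assumed.

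One thing survives these replies. For a component of the primary outcome, the single stated time does not secure answers from those who stop, and pairwise deletion would leave any gap unfilled.

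**Conclusion.** The point holds as a risk created by the stated timing, not as a demonstrated bias. Followed as written, the satisfaction summary may rest mainly on patients who stay to the end and may be too favourable.

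Up to 5 of 20 patients could be non-completers without a score while the retention criterion is met. The corresponding 25-point gap is a worst case that depends on yes/no scoring, on all five leaving early without being asked, and on none of them being satisfied. If nobody leaves early, the problem disappears.

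The lack of a link to t4 is a secondary ambiguity. The article does not place the questionnaire after surgery; it only fails to secure collection before it.

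In a descriptive pilot of this size the matter is modest. It is still worth settling, because it touches the primary outcome and cannot be repaired once patients have left unasked.

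**What to change.** Amend the satisfaction item to say that the existing questionnaire is given at t4, before surgery, or soon after the last attended session for participants who stop early. If the full protocol already provides for this, say so in the item.

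In the analysis, report satisfaction with the number responding out of all enrolled, and show early leavers separately from those who stayed to the end.

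The cost is one wording change and an existing questionnaire offered at discontinuation. The downside is that the figure may be less favourable and some early leavers will not respond; stating the number responding makes that visible.
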